### Concealment mechanism {16b}

Treatment administration will be done according to the randomization arm following the pre-established randomization list.

Sequentially numbered containers of methylprednisolone or placebo with identical appearance prepared by the pharmacy will be stored in the ICU. The computer randomization procedure will generate a container (kit box) number. The available container with the computer-generated number in the department’s stock will be assigned to the newly included patient in order to proceed with the randomization.

### Implementation {16c}

The randomization sequence of methylprednisolone versus placebo will be generated on the eCRF. The group assignment will then be provided to the investigator and the study coordinator.

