### Trial design {8}

CORTICOP is an investigator-initiated, phase 3, multicentre, parallel-group, double-blind, randomized (1:1), placebo-controlled trial comparing systemic corticosteroids versus placebo in patients admitted to an ICU for a severe acute exacerbation of COPD who require mechanical ventilation (invasive or NIV). The trial will be done in accordance with the Standard Protocol Items: Recommendations for Interventional Trial guidelines.

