### Intervention description {11a}

Randomization should be performed no later than 24 h after all inclusion and exclusion criteria have been completed.

Study drug (corticosteroid or placebo) should be administered no later than 4 h after randomization. Instructions for the reconstitution of the study drug are provided on a leaflet in the treatment kit.

In the experimental group, methylprednisolone will be administered intravenously for 5 days at a dose of 1 mg/kg/day. Methylprednisolone will be provided for reconstitution and dilution in 50 mL of NaCl 0.9% solution and administered over 15 min, once a day.

In the control group, placebo will be administered intravenously for 5 days. The placebo will be identical in appearance to the experimental substance. Placebo will be provided as 50 mL of NaCl 0.9% solution and administered intravenously over 15 min, once a day.

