## Assignment of interventions: blinding

### Who will be blinded {17a}

Trial participants, physicians in charge, nurses in charge, researchers involved in the study, and outcome assessors will be blinded.

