### Procedure for unblinding if needed {17b}

Unblinding will be permissible in case of severe adverse events.

Instances that require immediate unblinding will be handled according to the Versailles hospital standard operation procedures. For this blinded trial, an emergency procedure will be applied. Each pharmacy and/or local investigator will have an unblinding card for emergency management. The reason for breaking the code must be documented in the source document and on the eCRF page, along with the date and the initials of the person who broke the code. The sponsor must be informed as soon as possible of the unblinding by the centre.

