## Data collection and management

### Plans for assessment and collection of outcomes {18a}

The investigator and the study coordinator will be responsible for data collection.

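### Section 16c says the group assignment goes to the investigator and study coordinator, which contradicts the blinding stated elsewhere and has to be reconciled

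*Protocol article*

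**What the plan says.** All references are to the protocol article.

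- Trial design {8} describes a "phase 3, multicentre, parallel-group, double-blind, randomized (1:1), placebo-controlled trial".
- Concealment mechanism {16b}: "Sequentially numbered containers of methylprednisolone or placebo with identical appearance prepared by the pharmacy will be stored in the ICU". It continues: "The computer randomization procedure will generate a container (kit box) number". The container bearing that number is then given to the patient.
- Implementation {16c} says that the sequence of methylprednisolone versus placebo is generated on the eCRF, and then: "The group assignment will then be provided to the investigator and the study coordinator".
- Section 17a, on who is blinded, states: "Trial participants, physicians in charge, nurses in charge, researchers involved in the study, and outcome assessors will be blinded".
- Section 17b, on emergency code breaks, states: "Each pharmacy and/or local investigator will have an unblinding card for emergency management". Any code break must be documented with its reason and notified to the sponsor. Section 11b adds a secret code for each treatment container.
- Plans for assessment and collection of outcomes {18a}: "The investigator and the study coordinator will be responsible for data collection".
- Intervention description {11a} says that methylprednisolone is supplied for reconstitution and dilution in 50 mL saline. For the control arm: "Placebo will be provided as 50 mL of NaCl 0.9% solution and administered intravenously over 15 min, once a day". The same section calls the placebo identical in appearance. It also mentions a leaflet in the kit on reconstituting the study drug, a term it has just defined as covering either arm.

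**The concern.** In 16c the only thing assigned is methylprednisolone or placebo, so the natural reading of group assignment is the treatment arm. The two roles that receive it are the two that collect the data.

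The primary outcome is exposed to knowledge of the arm. Ventilator-free days count days off both invasive ventilation and NIV (section 12). Section 11d standardizes NIV withdrawal but leaves the clinician room to depart from the procedure, and leaves the extubation decision to the clinician. Section 11b leaves rescue corticosteroids to the attending physician, and section 22 lets the investigator continue or withdraw the assigned treatment after an adverse event. Someone who knew the arm could make any of these decisions differently without intending to.

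The article also lists double-blinding among its strengths, in contrast with earlier open-label trials. A sentence that permits disclosure of the arm undercuts that claim.

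**Working it through.** No formula applies and the plan gives no figure to reproduce. The check is whether the sections can all be followed at once, under each of two readings of 16c.

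| Section | If 16c means the arm | If 16c means the kit number |
|---|---|---|
| 8, double-blind design | Contradicted | Consistent |
| 16b, kit number generated, containers identical | Kit number would not protect the blind | Consistent |
| 17a, physicians, researchers and assessors blinded | Contradicted | Consistent |
| 11b and 17b, code break available to the local investigator | No purpose, since the arm is already known | Consistent |
| 18a, investigator and coordinator collect data | Data collectors unblinded | Data collectors blinded |
| 16c, its own wording | Matches | Does not match: it names the group, after a sentence naming the two arms |

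The kit-number reading fits every section except the sentence in question. The arm reading fits that sentence and conflicts with sections 8 and 17a. The kit-number reading is therefore the more likely intention, but a reader has to infer it. Section 16b already covers the kit number, and 16c then describes a further step in different words. Nothing in the text equates the two.

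Consequence of the literal reading:

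1. 16c gives the arm to the investigator and the coordinator.
2. 18a gives outcome data collection to the same two roles, and no separate assessor is named in 18a.
3. 17a requires researchers and outcome assessors to be blinded.
4. Steps 1 and 2 therefore breach step 3 for every randomized patient, which is 440 at the planned sample size.

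The second strand is kit presentation in 11a. Four statements stand together there: the active drug is supplied for reconstitution and dilution; the placebo is supplied as 50 mL of saline; the two look identical; and reconstitution instructions cover a study drug defined as either arm. A ready solution needs no reconstitution, so the second statement does not fit the fourth, and taken literally it sits badly with the third. Section 16b says that the pharmacy prepares the containers but that they are stored in the ICU, and the leaflet is inside the kit. The text therefore leaves open whether the final preparation happens on the ward, where 17a lists nurses as blinded.

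**The case against.** The strongest reply is that a single loose sentence cannot outweigh the rest of the document. The trial is called double-blind repeatedly, the mechanism runs on numbered identical containers, and the investigator has an emergency code break that would be pointless if the arm were known. On kit presentation, the leaflet covers both arms by the section's own definition. Both infusions are 50 mL of saline over 15 minutes once a day, and the differing sentences may simply describe contents. A condensed article may leave manufacturing detail to the full protocol.

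Much of this stands. A reader might infer from 16c that the trial is not double-blind, and the document does not support that: sections 8, 11b, 16b, 17a and 17b all describe a blinded trial. A reader might also infer from 11a that the kits can be told apart. That too is an inference, since the article says that they look identical.

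One further limit should be granted. The clinician's discretion over the rhythm and duration of NIV after extubation operates within each 24-hour period, and the outcome counts days, so this discretion need not move it. The relevant decisions are when NIV is withdrawn and when the patient is extubated.

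What remains is that the reply explains what the authors probably meant but does not change what 16c tells a site to do. The missing detail also does not excuse the contradiction, because the point concerns statements the article makes, not ones it omits.

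**Conclusion.** The point holds as an internal contradiction on blinding. Section 16c, read as written, cannot be followed together with sections 8 and 17a, and the roles it names are those that collect the outcome data under 18a. Section 11a is a secondary inconsistency of the same kind.

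The finding is not that the blind is broken. It is that the text permits disclosure to staff who must be blinded, in a trial whose primary outcome depends partly on clinical judgement. The potential reach is all 440 patients. The size of any bias cannot be computed, because the document gives no basis for how far weaning decisions or recording would shift with knowledge of the arm. No alpha, power or sample size figure is affected.

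The contradiction itself rests on the wording alone. The concern about weaning decisions further assumes that investigators take part in, or communicate with, the team making those decisions, which the document does not state outright. The concern about data collection needs only 16c and 18a.

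The correction is warranted because it is specific, nearly free, and protects the feature on which the trial's added value rests.

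**What to change.** 1. In 16c, replace the sentence on group assignment with wording such as: *The system releases only the kit number. The investigator, the study coordinator and all other site staff remain blinded to the arm, except through the procedure in section 17b.*
2. Check that the randomization screen, confirmation messages and any automatic notifications show no arm.
3. If the check shows that the arm is in fact released, correct 17a and the double-blind label instead, and say who knows the arm.
4. In 11a, reconcile the supply and reconstitution statements so that the presentation and preparation described are the same in both arms. Alternatively, state that the pharmacy, outside the blinded team, does the preparation.

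The cost is a few sentences in 16c and 11a plus one check of the randomization system. If only kit numbers are displayed and the kits already match, nothing operational changes.

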## Assignment of interventions: blinding

### Who will be blinded {17a}

Trial participants, physicians in charge, nurses in charge, researchers involved in the study, and outcome assessors will be blinded.

### Procedure for unblinding if needed {17b}

Unblinding will be permissible in case of severe adverse events.

Instances that require immediate unblinding will be handled according to the Versailles hospital standard operation procedures. For this blinded trial, an emergency procedure will be applied. Each pharmacy and/or local investigator will have an unblinding card for emergency management. The reason for breaking the code must be documented in the source document and on the eCRF page, along with the date and the initials of the person who broke the code. The sponsor must be informed as soon as possible of the unblinding by the centre.

## Data collection and management

### Plans for assessment and collection of outcomes {18a}

The investigator and the study coordinator will be responsible for data collection.

### Plans to promote participant retention and complete follow-up {18b}

No participants will be lost to follow-up providing they remain in the hospital. Before hospital discharge, patient information, including their telephone number and those of their relatives will be noted in their personal medical file to ensure the completion of follow-up at day 90.

### Data management {19}

Designated staff will enter the data into the eCRF under the supervision of the principal investigator in each centre, who will be responsible for ensuring that the data collected are complete, accurate, and that entry is performed in a timely manner. A data manager will be in charge of checking missing or inconsistent data, and providing queries to be solved. In case of missing data, the reason will be noted. Corrections, with the reason for the corrections, will also be recorded/tracked in the eCRF.

After resolution of all queries, the database will be locked for statistical analysis.

### Confidentiality {27}

Participants included in this research will be identified using a unique anonymous reference number that will be used for the entire duration of the study. For eligible patients who are not included in the study, the date and reason for non-inclusion will be anonymously collected in order to build a patient flow chart.

All study-related information will be stored securely at the study site. All participant information will be stored in locked filing cabinets in areas with limited access. All reports, data collection, processes, and administrative forms will be identified only by a coded identification number to maintain participant confidentiality. All records that contain names or other personal identifiers, such as locator forms and informed consent forms, will be stored separately from study records identified by code number.

Data will be handled according to French law on data protection and European General Data Protection Regulation (GDPR). All original records will be archived at trial sites for 15 years.

### Plans for collection, laboratory evaluation and storage of biological specimens for genetic or molecular analysis in this trial/future use {33}

Not applicable, as no specimens will be collected.

## Statistical methods

### Statistical methods for primary and secondary outcomes {20a}

All analyses will be performed by the study statistician according to a predefined statistical analysis plan, using the latest versions of R software© (R Foundation for Statistical Computing, Vienna, Austria) or Statistical Analysis System© (SAS). A two-tailed *p* value of less than 0.05 will be considered as indicating statistical significance.

In accordance with the CONsolidated Standards Of Reporting Trials (CONSORT) statement, a flow diagram will describe the progress of patients in the two groups through the phases of the trial (enrolment, intervention allocation, intervention received, follow-up and data analysis). The analysis will be performed on an intention-to-treat basis. In case of premature stop or withdrawal from the study, patients will not be substituted. Missing values will be described and, according to nature and frequency, multiple imputation methods will be used. A per-protocol analysis will be used as a sensitivity analysis, excluding patients who were wrongly randomized or did not receive the allocated intervention. Comparative analysis will systematically be done with (main analysis) and without adjustment on randomization stratification factors.

Quantitative data will be described as means, medians, standard deviations, and interquartile ranges. Nominal data will be described as percentages with 95% confidence intervals. Proportions of missing data will be given. Patient characteristics will be described by centre and compared. Quantitative data will be compared using *t*-tests or non-parametric tests (Mann–Whitney sum rank) when the distribution does not approach symmetry even after suitable transformation (Tukey’s ladder of powers). Qualitative data will be compared by means of chi-square tests or Fisher exact tests. Time-to-event data (survival) will be described using Kaplan–Meier curves.

The analysis of the primary outcome (i.e., distribution of VFDs that is highly skewed) will be performed by a multivariate non-parametric test, taking into account stratification and minimization criteria used in the randomization [21]. The final test will be performed at a 0.049 two-sided alpha risk to guarantee a global 5% alpha level.

The main analysis will be performed according to the intention-to-treat principle on the full dataset, while analyses on imputed data dealing with missingness will be considered as sensitivity analyses. As a secondary analysis, a time-to-event model, where death and becoming ventilator free are competing risks, with a fixed factor corresponding to the randomization arm, centre being considered as a random factor, taking into account other prognostic factors and their interactions with the randomized treatment, will be developed.

The analysis of the effect of the intervention on secondary criteria: mortality, adverse events, and length of ventilation, will be performed using generalized linear model regression. The link function and distribution of errors will be chosen according to the nature of the response: logistic and binomial if the response is binary (mortality), identity and Gaussian if the response is considered continuous. Time-to-event censored data (becoming ventilation free or death being competing risks) will be analysed by piecewise exponential regression models. The main secondary analyses will firstly be stratified on randomization criteria without further adjustment then, after bivariate screening, the main confounders (*p* value < 0.2 or retrieved from the literature) and interactions with treatment will be tested in a multivariable model. The shape of the relationship of continuous factors will be explored by fractional polynomials. Goodness-of-fit will be verified (influential observations, R2, discrimination, calibration) and performance of the models will be assessed by Akaike information criteria.

These analyses will be performed on the intention-to-treat groups, except for safety or tolerability criteria, which will be analysed on per-protocol populations.

Analyses will be performed in the NIV or invasive ventilation subgroup (prespecified in the analysis plan) to assess the homogeneity of the difference between the two treatment groups. These subgroup analyses will be supplemented by interaction tests between the treatment and the subgroup variables using Breslow & Day tests. The results will be graphically presented using Forest plots.

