### Outcomes {12}

#### Primary outcome measure

Number of ventilator-free days (VFDs) at day 28 is defined as the number of days alive without mechanical ventilation (invasive and/or NIV) between randomization and day 28.

VFDs are defined as follows:VFDs = 0 if the patient dies before 28 days or the patient requires mechanical ventilation for ≥ 28 daysVFDs = 28 − x if the patient is successfully weaned from mechanical ventilation within 28 days, where *x* is the number of days spent receiving mechanical ventilation (invasive and/or NIV).

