### Sample size {14}

Based on a large database that included 35 ICUs [3], the mortality rate associated with severe acute exacerbations of COPD is 17% and the mean duration of ventilation (invasive or NIV) is 5.8 days for alive patients (median 4 days). According to this database and previous published studies, 75% of patients are treated with NIV, while 25% are treated with invasive mechanical ventilation. We performed several simulations in which we varied the mortality rate (binomial, 15–19%) and the mean duration of ventilation (log-normal distribution, 5–7 days) and calculated the required sample size according to alpha risk = 5% and beta risk = 20% and various hypotheses of efficacy (none or 1% reduction in the mortality rate, combined with a 2–4-day reduction in days of ventilation) and a Wilcoxon test of the resulting VFD in the two groups. It showed that 200 patients per group would allow the detection of at least a 2-day reduction in ventilation regardless of the impact on mortality. Accounting for withdrawal of consent, a 10% increase was allowed, i.e. a sample size of 220 per group, for a total of 440.

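### Length of ventilation has both a Gaussian regression with no rule for deaths and a competing-risks analysis, with neither named as main; NIV failure does not count death without intubation

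*Protocol article*

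**What the plan says.** **Duration of ventilation.** Secondary outcome measures lists the duration of invasive ventilation and the total duration of ventilation, without saying what value a patient who dies receives. In Statistical methods {20a}, the effect on "secondary criteria: mortality, adverse events, and length of ventilation, will be performed using generalized linear model regression". The link and error depend on the type of response: logistic and binomial if binary, "identity and Gaussian if the response is considered continuous". These analyses use the intention-to-treat groups, except for safety and tolerability criteria.

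The next sentence adds a second analysis of nearly the same quantity: "Time-to-event censored data (becoming ventilation free or death being competing risks) will be analysed by piecewise exponential regression models". Earlier in the section, a secondary analysis to the primary outcome is described as "a time-to-event model, where death and becoming ventilator free are competing risks". Nothing says which result is the main one for duration.

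**Distribution.** Sample size {14} simulates "the mean duration of ventilation (log-normal distribution, 5–7 days"), and gives a mean of 5.8 days and a median of 4 days in survivors, with 17% mortality.

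**NIV failure.** Objectives {7} and Secondary outcome measures both define it as a need for intubation in the first 7 days after randomization. Death is not part of the definition.

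**Contrast.** The primary outcome does have a death rule: "VFDs = 0 if the patient dies before 28 days".

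**The concern.** Ventilation ends either by weaning, which is good, or by death, which is not. A regression of the raw number of days treats both endings alike. A patient who dies on the ventilator on day 2 enters as about 2 days, below the survivors' median of 4. If mortality differs between arms, the difference in mean duration is no longer a difference in speed of weaning. Because a competing-risks analysis stands beside the regression without an order between them, the two could point in different directions and the plan would not say which to believe.

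An identity-link Gaussian model also sits poorly with the log-normal shape that the protocol assumes for the same variable.

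For NIV failure the issue is simpler. Someone who dies on NIV by day 7 without being intubated is recorded as not having failed.

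**Working it through.** **Inputs from the protocol.** Sample size {14}: mortality 17%; survivors' duration log-normal, mean 5.8, median 4; 200 evaluable and 220 randomized per arm; 75% treated with NIV; planned effect a 2-day reduction.

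**The plan's own figure.** 200 × 1.10 = 220 per arm, and 2 × 220 = 440. This reproduces, and the point does not depend on it.

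**Shape of duration.** Log-scale SD = √(2 ln(5.8/4)) = 0.862. Capped at 28 days, the mean becomes 5.8 × Φ(2.257 − 0.862) + 28 × (1 − Φ(2.257)) = 5.66 days, where 2.257 = ln(28/4)/0.862.

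**Bias in mean duration: a simple model.** Assume no treatment effect on weaning, ventilation that continues until death in those who die, and exponential time to death (capped at 28 days). Then

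shift = (excess mortality) × (mean time to death − 5.66).

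The protocol gives neither an excess mortality nor the timing of deaths, so both are assumptions:

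| Mean time to death | 22% v 17% | 27% v 17% |
|---|---|---|
| 1 day | −0.23 | −0.47 |
| 3 days | −0.13 | −0.27 |
| 5 days | −0.03 | −0.07 |
| 7 days | +0.06 | +0.12 |
| 10 days | +0.19 | +0.37 |

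Negative values mean that the arm with more deaths looks better. Simulation agrees to within 0.01 day. The sign changes when the mean time to death passes the mean duration in survivors, between 5 and 7 days here.

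**A second model.** Suppose patients who die would have needed twice the usual ventilation, cut short by death or weaning, whichever comes first. With 22% v 17% mortality the shift is −0.16 day at mean death day 3, about −0.10 at day 5, about zero at day 10, and slightly positive at day 14.

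**Scale.** With an SD of about 5.2 days and 220 per arm, the standard error of the difference is 5.2 × √(2/220) = 0.50 day. A shift of 0.10 to 0.16 day is therefore 0.2 to 0.3 standard errors.

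**Efficiency.** Survivors per arm: 0.83 × 200 = 166. Simulated two-sided 5% t-tests, durations capped at 28 days, log-scale SD 0.862 in both arms:

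| Mean duration | Raw days | Log days |
|---|---|---|
| 5.8 to 4.8 | about 42% | about 51% |
| 5.8 to 4.3 | about 79% | about 89% |
| 5.8 to 3.8 (planned effect) | about 97% | about 99% |

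**NIV failure.** 0.75 × 220 = 165 NIV patients per arm, taking the 75% as the share in the NIV stratum. One unintubated death by day 7 changes the rate by 1/165 = 0.6 percentage points relative to a composite of intubation or death. The protocol does not say how many such deaths to expect. If 3% to 8% of the 330 NIV patients in both arms died this way (assumed), 10 to 26 would be recorded as not failing. That is a count across the trial and not a difference between arms.

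**The case against.** The strongest reply is that death is already handled. The competing-risks analyses in the same section treat it correctly for essentially the same quantity, mortality is reported separately at four time points, and the primary outcome gives death the worst score. This largely stands. What remains is that length of ventilation is assigned by name to the regression and no order is set between the two analyses.

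Second, a reader might infer that the protocol scores death as a favourable value. It does not say so. It is silent on how deaths enter duration, and the unseen analysis plan may restrict duration to survivors or censor deaths. The calculation also shows that the advantage to the arm with more deaths appears only when deaths are early, and reverses when they are late.

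Third, a reader might infer that the Gaussian model would miss a real effect. At the planned 2-day effect it loses about 2 points of power. The Gaussian choice is also conditional, goodness-of-fit checks are required, and the general methods paragraph allows transformation or rank tests for asymmetric data. The conditional wording does not settle the matter, because of the two response types that the section spells out, binary and continuous, only the second suits a duration.

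Fourth, intubation within 7 days is a recognizable endpoint, defined consistently, and its name implies patients on NIV. So the absence of an explicit denominator is not a defect in itself. A composite is a different estimand, and no difference between arms has been shown. That is fair, but the recorded rate still cannot rise because of an unintubated death.

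**Conclusion.** The point holds in a limited form. Length of ventilation has two planned analyses, one of which mixes weaning with death, and the protocol does not rank them. Under the assumed inputs the resulting bias is small: at 5 points of excess mortality, at most about a quarter of a day in either direction, even with a mean time to death as short as 1 day. Its sign depends on the timing of deaths, which the protocol does not give. That uncertainty of sign is itself a reason not to read the mean difference as a treatment effect. The loss of efficiency matters mainly for effects below 2 days.

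For NIV failure the direction is fixed, at about 0.6 points per unintubated death in an arm of 165, but the number of such deaths is unknown.

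Neither matter touches the primary analysis. They concern the interpretation of two secondary outcomes, and the change is worth making because it is cheap.

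**What to change.** 1. Name the competing-risks model already planned as the main analysis of duration of ventilation, and report cumulative incidence of becoming ventilator-free and of death by arm. Report durations in survivors as median and interquartile range, without a Gaussian test.
2. Analyse NIV failure as intubation or death within 7 days among patients randomized in the NIV stratum, with intubation alone shown as a component.

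Cost: a few sentences and one derived variable. No new data are needed, since Table 1 already schedules ventilation and vital status daily. The drawback is that the composite is less directly comparable with studies that count intubation only; the component row meets this.
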